#### **10.4 Other study parameters**

Not applicable.

#### **10.5 Interim analysis**

With respect to safety, an independent statistician will perform unblinded interim analyses on reported SAE and AE after 150 and 300 patients have completed the 90 days post-stroke follow-up.

## **11. ETHICAL CONSIDERATIONS**

### **11.1 Regulation statement**

Study conduct will be according to the principles of the Declaration of Helsinki (64th WMA General Assembly, Fortaleza, Brazil, October 2013) and in accordance with the Medical Research Involving Human Subjects Act (WMO). TMS procedures will be performed according to expert guidelines on safety and recommendations for TMS use in healthy subjects and patient populations.

### **11.2 Recruitment and consent**

Patients potentially eligible for participation will be approached by the treating rehabilitation physician. The treating rehabilitation will ask the patient whether the local investigator can approach him or her. Patients will be screened for eligibility by the local investigator based on the inclusion and exclusion criteria, which includes eligibility according to the TMS safety questionnaire. If the patient is eligible, the local investigator explains the study procedures and provides the eligible patient with the patient information letter. The local investigator encourages the patient to read the information, discuss the content with friends or relatives and to write down questions that may arise. The patient will be given time to consider participation. During a second consultation with the local investigator, the investigator will give the patient the opportunity to ask questions, after which the patient can provide written informed consent. In case the patient does not have the capacity to provide written informed consent (e.g., due to upper limb impairments or aphasia), his/her representative may provide written informed consent. As soon as the patient has regained capacity, he/she will be asked for written informed consent. The patient will be provided with a copy of the signed informed consent.

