### 4.2 Inclusion criteria

To be eligible to participate in this study, a participant must meet all the following criteria:

- Age, 18 years or older
- First-ever unilateral ischemic stroke or intracerebral hemorrhage in a cerebral hemisphere or in the brainstem;
- Unilateral upper limb paresis with a motricity index between 9 and 99;
- Possibility to start cTBS treatment within 21 days after stroke onset;
- Signed informed consent.

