### 4.3 Exclusion criteria

A potential subject who meets any of the following criteria will be excluded from participation in this study:

- Upper limb paresis prior to stroke onset;

- Absolute contra-indication to TMS
  - Magnetically sensitive objects implanted in or guided through the head or neck area (e.g. cochlear implants, implanted neurostimulator, pacemaker or defibrillator leads, metal splinters, metal fragments or metal clips) with the exception of dental work (e.g. fillings, braces or implants);
  - History of epilepsy;
  - Pregnancy;
  - Other contra-indications that may potentially be harmful as determined by the treating rehabilitation physician;
- Incapacity or severe impairments (i.e. extreme fatigue, major communication deficits) that can impede study participation as determined by the treating rehabilitation physician;
- Life expectancy shorter than one year.

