### **Stroke Impact Scale**

The Stroke Impact Scale (SIS) is a self-report questionnaire for the evaluation of disability and health-related quality of life after stroke. Three sections that are directly or indirectly related to upper limb recovery will be assessed: hand function, participation and overall recovery.

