### **11.3 Objection by minors or incapacitated subjects (if applicable)**

Not applicable.

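### Protocol 11.2 lets a representative consent for a patient whose arm is too weak to write, and foresees participants without capacity whom 4.3 and 11.3 do not provide for

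*Combined protocol and SAP*

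**What the plan says.** Five parts of the protocol bear on who may consent and who may enter.

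- **4.2, arm function.** Every participant must have "Unilateral upper limb paresis with a motricity index between 9 and 99".
- **4.2, consent.** The criterion reads "Signed informed consent" and does not say whose signature is meant.
- **4.3.** The relevant exclusion is "Incapacity or severe impairments (i.e. extreme fatigue, major communication deficits) that can impede study participation as determined by the treating rehabilitation physician".
- **11.2.** Where a patient "does not have the capacity to provide written informed consent (e.g., due to upper limb impairments or aphasia), his/her representative may provide" the written consent instead. The section continues: "As soon as the patient has regained capacity, he/she will be asked for written informed consent".
- **11.3.** The section headed "Objection by minors or incapacitated subjects (if applicable)" contains only the statement that it is not applicable.

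Section 11.2 also fixes an order: the local investigator screens against the inclusion and exclusion criteria, and only eligible patients go on to information and consent.

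**The concern.** Two things in 11.2 do not fit the rest of the protocol.

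First, it gives weakness of the arm as an example of lacking capacity to consent. A patient who cannot write because the writing hand is paretic can still understand, weigh up and decide. The difficulty lies in recording the decision. In a trial where arm paresis is required for entry, this example concerns the core population.

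Second, it provides for enrolling someone without capacity and seeking their own consent later. Section 11.3 is written as if there will be no such participants, and 4.3 excludes at least some of them.

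At stake are the validity of consent, the protection of participants who cannot speak for themselves, and consistent eligibility for patients with aphasia across the 16 centres named in SAP section 2. There is also a data question. The Stroke Impact Scale is described in protocol 8.3 as a "self-report questionnaire for the evaluation of disability and health-related quality of life after stroke". The EQ-5D-5L is likewise a questionnaire, the patient's guess at treatment allocation is recorded, and the cost questionnaires address the patient directly. No proxy version, and no rule for a participant unable to answer, is given.

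**Working it through.** No figure in the plan depends on this point. The total of 440 in section 4.4 does reproduce: a difference of 6.6, SD 23, two-sided alpha 0.05 and power 0.85 give 219.03 per arm by t-test, rounded up to 220, and 2 × 220 = 440. None of those inputs is touched here. The check is therefore a comparison of the texts.

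**Step 1: what capacity means in 11.2.** There are two candidate readings.

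- *Ability to decide.* Aphasia fits as an example, and so does the sentence about regaining capacity. Arm impairment does not fit, because it does not affect decision-making. On this reading 11.2 plans for incapacitated participants, so marking 11.3 not applicable is inconsistent with it.
- *Ability to complete a written form.* Arm impairment now fits, and 11.3 can stand. But 11.2 has the representative give the consent. It does not have the representative witness or record the patient's own decision, so a competent patient's consent is replaced by another person's. The sentence on regained capacity also fits poorly: the patient's own agreement would wait until they could write, although it could have been obtained at the start.

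Neither reading makes 11.2 and 11.3 agree and also keeps the decision with a patient who can decide.

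**Step 2: whether the qualifier in 4.3 resolves it.** The words about impeding participation can attach in two ways.

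- *To severe impairments only.* Then all incapacity is excluded. The representative route has no incapacitated patient left to serve, and only competent patients remain to pass through it.
- *To incapacity as well.* Then some patients without capacity are eligible and the route has a use. In that case 11.3 is applicable and needs content.

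Either way one of the sections has to change.

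**Step 3: aphasia.** Section 4.3 excludes major communication deficits that impede participation, on the treating physician's judgement. Section 11.2 gives aphasia as a ground for representative consent. No section says how severe aphasia must be to count as major. Two centres could therefore judge the same patient differently and each be following the protocol.

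**Step 4: reach into the analysis.** Randomisation is stratified by centre (protocol 8.2). The primary model has a random effect for centre (protocol 10.2, SAP 7.4). The FM-UE is a performance test scored by certified assessors. Differences between centres in who is admitted would fall on both arms within a centre, so they do not bias the primary comparison. What is left is consent, consistency of eligibility, and the quality of self-reported secondary and cost data.

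**The case against.** The best defence has four parts.

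**The order of steps.** Section 11.2 applies the eligibility criteria before consent is reached, so 4.3 is not an alternative to 11.2 that a site may choose to ignore. This stands. A reader might infer that the same patient will be excluded at one site and enrolled at another, so that centres will recruit different populations. The documents do not support that. They support only that handling may differ, because the boundary for aphasia is undefined and left to judgement.

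**The benign reading.** Capacity may have been meant only as the ability to complete the form. The rest of the paragraph, in which the patient is approached, informed, given time and invited to ask questions, gives this some weight. It does not rescue the text, for the reasons in step 1 of the working.

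**Existing safeguards.** Protocol 8.4 lets any subject leave at any time, section 11.1 commits the trial to the Dutch research act and the Declaration of Helsinki, and SAP 5.2 imputes missing data. These soften the consequences. But the right to leave is framed around a subject's own wish and does not say how resistance by a person without capacity is to be recognised. Imputation does not settle whether answers given by someone else are accepted. The consent form was not available for this review and may already allow for witnessed consent. If it does, 11.2 should say so.

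**Scale.** A reader might infer that a large share of the 454 patients is affected, since all have a paretic arm. A Motricity Index of 9 to 99 includes mild weakness, and paresis is not inability to sign. The documents give no rate for either inability to write or aphasia, so any count would be an assumed percentage multiplied by 454. A reader might also infer that data would have to be removed because of defective consent. Nothing in the documents says so.

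**Conclusion.** The point holds in a limited form. As written, 11.2 permits a representative to consent in place of a patient who is able to decide, on the ground of arm weakness. It also anticipates participants without capacity, for whom 11.3 makes no provision and whose eligibility under 4.3 is unclear. For patients with aphasia, practice may vary between centres.

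The size cannot be given. The conclusion rests on the wording of 4.2, 4.3, 11.2 and 11.3 and on one plain premise, that weakness of an arm does not by itself remove the ability to decide. The sample size is unaffected and the primary comparison is not biased. Whether patients without capacity should be enrolled at all is for the sponsor to choose, and the documents do not settle it.

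**What to change.** 1. In 11.2, remove arm impairment as a ground for representative consent. State that a patient who can decide but cannot write gives their own consent, recorded in another way, for example orally or by a mark before a witness who signs.
2. Make 4.2, 4.3, 11.2 and 11.3 agree by one of two routes:
   - limit consent to the patient, say so in 4.2, and remove the representative route from 11.2; or
   - keep the representative route, state in 4.3 which incapacity (including what degree of aphasia) is still eligible, complete 11.3 with an objection procedure, and state how the self-reported outcomes and cost questionnaires are handled for those participants, either as missing or by a named proxy version.

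The cost is a short protocol amendment and, if the consent form does not already have one, a witness line. Under the first route a few patients who could have entered through a representative may no longer be enrolled. The second route keeps them but needs more text and a data-handling rule in the SAP and the health-economic plan. The change is best made early, since consent is hard to repair after enrolment.

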### **11.3 Objection by minors or incapacitated subjects (if applicable)**

Not applicable.

### **11.4 Benefits and risks assessment, group relatedness**

Data from our phase II trial (B-STARS) show that cTBS treatment leads to a clinically relevant improvement in upper limb recovery, with 17% (n 60; 9.6 points; 95%CI 1.2–17.9) additional recovery of upper limb activity, as measured with the ARAT three months after stroke. This additional recovery led to a significant improvement in activity and participation (of similar magnitude) and a reduction in the length of stay at the rehabilitation center by 18 days on average.

cTBS treatment only led to mild side effects, such as headache (<4%) and muscle pain (<1%) and was reported to be tolerable and comfortable. The risk of inducing an epileptic seizure is very small (0.02%) and consequences of an epileptic seizure can be mitigated by adequate training of personnel. The risk of experiencing an epileptic seizure in the early phase after stroke (not induced by TMS) varies from 2 to 12%. Therefore, rehabilitation centers have protocols in place. TMS-therapists are instructed to adhere to local protocols in case of an epileptic seizure. We are aware that including patients in a clinical trial in the early stages of recovery imposes a burden on them. However, evidence shows that treatment is most likely to be effective in the early post-stroke phase.

Therefore, cTBS treatment is likely to have a clinically relevant benefit, while the risk and burden of participation are negligible.

### **11.5 Compensation for injury**

The sponsor/investigator has liability insurance in accordance with article 7 of the WMO.

The sponsor (also) has an insurance which is in accordance with the legal requirements in the Netherlands (Article 7 WMO). This insurance provides cover for damage to research subjects through injury or death caused by the study.

The insurance applies to the damage that becomes apparent during the study or within 4 years after the end of the study.

### **11.6 Incentives (if applicable)**

Patients do not have any special incentive to participate in this study.

Travel costs for study participation are compensated for when patients are discharged from the rehabilitation center during follow-up.

## **12. ADMINISTRATIVE ASPECTS, MONITORING AND PUBLICATION**

### **12.1 Handling and storage of data and documents**

All personal data will be handled confidentially according to the EU General Data protection regulation (GDPR) and the Dutch General data Protection Regulation (AVG). Each participant will be allocated an identification code as part of the randomization procedure. Only the local investigator has access to the key table that links the identification code to the participant's personal information. The key table will be encrypted and stored on a local hard drive in the rehabilitation center.

Non-personal study data will be entered into CASTOR through an eCRF by the investigator who included the participant, or by his/her local representative. The participant's email address will be submitted in CASTOR separately. The email address is used to send out medical consumption and productivity questionnaires 6 months after stroke.

Informed consents, questionnaires, and forms on treatment parameters and motor function tests and the EMG data will be stored at the local archive of the rehabilitation center and will be safeguarded by the local investigator. Data from the paper forms will be entered into CASTOR through an eCRF by the investigator who performed the treatment or assessment, or by a representative. Anonymous EMG data will be transferred to the UMC Utrecht through SURFfilesender using encryption. The raw data will be stored for as long as the data is used for research purposes and for 15 years minimally.

The combined dataset in CASTOR from all participating centers can only be accessed by the coordinating investigators. Local investigators will be provided with a subset of the data in CASTOR that was acquired at their study site.

### **12.2 Monitoring and Quality Assurance**

This study has a negligible risk, based on the risk classification of the Dutch Federation of University Medical Centers (NFU). Intensity of monitoring is based on the risk classification. Monitoring will be done by an independent and qualified monitor. This person is not involved in the design and execution of the study. Details can be found in a separate monitoring plan (K6).

### **12.3 Amendments**

Amendments are changes made to the research after a favorable opinion by the accredited METC has been given. All amendments will be notified to the METC that gave a favorable opinion.

### **12.4 Annual progress report**

The sponsor/investigator will submit a summary of the progress of the trial to the accredited METC once a year. Information will be provided on the date of inclusion of the first subject, numbers of subjects included and numbers of subjects that have completed the trial, serious adverse events/ serious adverse reactions, other problems, and amendments.

### **12.5 Temporary halt and (prematurely) end of study report**

The investigator/sponsor will notify the accredited METC of the end of the study within a period of 8 weeks thereafter. The end of the study is defined as the last patient's last visit. The sponsor will notify the METC immediately of a temporary halt of the study, including the reason of such an action. In case the study is ended prematurely, the sponsor will notify the accredited METC within 15 days, including the reasons for the premature termination. Within one year after the end of the study, the investigator/sponsor will submit a final study report with the results of the study, including any publications/abstracts of the study, to the accredited METC.

### **12.6 Public disclosure and publication policy**

The trial is registered in a public clinical trial registry ([clinicaltrials.gov](https://clinicaltrials.gov)) with identifier: NCT06265766. Results of this trial will be disclosed and published as an open access article in peer-reviewed international scientific journals.

## **13. STRUCTURED RISK ANALYSIS**

### **13.1 Potential issues of concern**

a. Level of knowledge about mechanism of action

A single TMS pulse can activate cortical neurons through electromagnetic induction. Repetitive delivery of TMS pulses can increase or reduce activity and excitability in the stimulated area depending on the stimulation paradigm, through long-term potentiation or depression (LTP/LTD) mechanisms, respectively. Stimulation paradigms such as low-frequency stimulation and continuous theta burst stimulation have been shown to reduce activity and excitability in the stimulated area. The effects of stimulation are not restricted to the stimulated area, but spread to connected brain regions.

The exact mechanism of rTMS treatment in promoting upper limb recovery is unclear. Previous neuroimaging and neurophysiological studies indicate that a motor stroke affects the balance in bilateral M1 activity, with the magnitude of the imbalance correlating with the level of impairment. Based on this evidence, it has been hypothesized that reducing contralesional M1 activity with inhibitory rTMS can promote recovery of the affected upper limb. Our phase II trial data show that inhibitory rTMS of the contralesional M1 promotes recovery of the upper limb. We also showed that treatment was associated with an increase in ipsilesional M1 excitability directly after 10 treatment sessions, providing a potential treatment mechanism.

b. Previous exposure of human beings with the test product(s) and/or products with a similar biological mechanism

TMS was invented in 1985 by Anthony Barker, after which it has been used to safely stimulate and study human motor cortex for over 35 years. TMS has been used repetitively for therapeutic purposes since its approval for the treatment of depression in 2008. Since then, several other clinical applications have been introduced, resulting in an abundance of TMS safety data.

c. Can the primary or secondary mechanism be induced in animals and/or in ex-vivo human cell material?

Yes, promotion of upper limb recovery with contralesional inhibitory rTMS can be studied in animals but not in ex-vivo human cell material.

d. Selectivity of the mechanism to target tissue in animals and/or human beings

TMS using a figure-of-eight coil results in a relatively focal effective stimulation area of roughly 1cm^3 of cortical tissue. This allows specific targeting of the M1 hand area, but does not rule out activation of neurons in premotor or sensory areas.

e. Analysis of potential effect

Data from our phase II trial (B-STARS) indicate that cTBS treatment results in 17% (n = 60; 9.6 points; 95%CI 1.2–17.9) additional recovery of upper limb function, as measured with the ARAT three months after stroke. This improvement exceeds the minimal clinically important difference of 10%. This additional recovery led to a significant improvement in activity and participation (of similar magnitude) and a reduction in the length of stay at the rehabilitation center by 18 days on average. In the current phase III trial, the potential effect will be analyzed with a similar selection of measurement tools to assess upper limb impairment and activity, disability and dependence and quality of life.

Our phase II trial data show that inhibitory rTMS only led to mild side effects, such as headache (<4%) and muscle pain (<1%). The current trial will assess side-effects of cTBS during treatment and within 1 week thereafter.

#### f. Pharmacokinetic considerations

Not applicable.

#### g. Study population

The study population consists of stroke patients who are in the early subacute phase of their recovery (within 3 weeks after stroke onset). This means that the study population consists of patients who are in the early stages of their recovery from a severe health condition. However, the early start of treatment is required for optimal treatment efficacy. A meta-analysis from our group and a guidelines paper show that treatment efficacy is likely to be optimal when rTMS treatment is started within 1 month after stroke onset. Our phase II trial data, in which treatment was started within 3 weeks after stroke onset confirm these findings. Moreover, the rTMS treatment induces only minimal strain on the subjects, due to the short duration (10 minutes preparation and 40s treatment duration) and comfortable setting (patients are seated in a reclining chair and don't have to perform an activity). Interviews with a selected number of subjects of the phase II trial revealed that cTBS was very tolerable and in some cases even provided a moment of relaxation in an otherwise busy rehabilitation program.

